**Results:**

A total of 10,013 participants were randomized, and the recruitment process started on 9 March 2023. Secondary outcomes include (i) moderate COPD exacerbations; (ii) all-cause hospitalization; (iii) ICU admission; (iv) need for non-invasive ventilation; and (v) all-cause mortality, among others. All outcomes will be evaluated 12 months after recruitment.

**Clinical trial registration:**ClinicalTrials.gov, NCT05563675.

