### Outcomes

The primary efficacy endpoint is the occurrence of hospitalization requiring AECOPD or death from all causes within 12 months. Secondary efficacy endpoints included (i) moderate COPD exacerbations; (ii) all-cause hospitalization; (iii) ICU admission; (iv) need for non-invasive ventilation; (v) all-cause mortality; (vi) SABA use/pick-up rate; and exploratory endpoints (i) relation between adherence and AECOPD hospitalization, (ii) change in CAT score, (iii) change in MRC score, and (iv) change in “soundly sleeping” parameter of CAT.

The details on the primary and secondary outcomes of the study can be seen in Tables 1, 2, and exploratory outcomes in Table 3.

**Table 2 tab2:** Secondary and exploratory endpoint definition.

Endpoint	ICD-10/ATC codes	Inpatient/outpatient/minimum required length of stay/other criteria
Moderate COPD exacerbations	Prednisolone: H02AB06 or Antibiotics: J01CA04, J01AA02, J01CR02, J01MA14	Excluding hospitalizations and emergency room visits: DJ441 (A)
Hospitalization (all-cause)		Inpatient, length of stay ≥24 h
Hospitalization in ICU (all-cause)		Inpatient, ICU, length of stay ≥24 h
Need for NIV	BGDA1	A or B
Mortality (all-cause)		Participant registered as dead in the CPR register.
SABA use/pick-up rate	R03AC02, R03CC02, R03AC03	Danish National Prescription Registry
Change in CAT score	Questionnaire	At 6 and 12 months
Change in MRC score	Questionnaire	At 6 and 12 months

The time frame is ≥1 day after randomization until the end of the study (12 months from randomization) for all outcomes. A = primary discharge diagnosis and B = secondary discharge diagnosis. COPD, chronic obstructive pulmonary disease; ICU, intensive care unit; NIV, non-invasive ventilation; CPR, Central (National) Person Registry; SABA, short-acting beta-2 agonists; CAT, COPD assessment test.

**Table 3 tab3:** Exploratory endpoint definition.

Endpoint	Data source or ICD-10 codes	Inpatient/outpatient/minimum required length of stay/other criteria
Relation between adherence and hospitalization-requiring AECOPD	Questionnaire, DJ440, DJ441	For hospitalizations: Type A diagnosis (primary discharge diagnosis). Inpatient and length of stay ≥24 h, or emergency room visits. Deaths excluded.
Change in CAT score	Questionnaire	At 6 and 12 months
Change in MRC score	Questionnaire	At 6 and 12 months
Change in CAT “soundly sleeping” parameter	Questionnaire	At 6 and 12 months

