## Statistical methods

### Statistical methods for primary and secondary outcomes

The primary and all secondary outcomes will be analyzed using the intention-to-treat (ITT) approach, which encompasses the entire cohort of randomized participants in the study. Additionally, per-protocol analyses will be conducted for patients taking inhalation medication 6–7 days per week at the allocated administration time for the full duration of the study, along with modified ITT (mITT) analyses for those who have taken less than 6 days or more than 2 days per week for any amount of time. These analyses will be performed on both the primary and all secondary outcomes, providing a comprehensive evaluation of the study’s results.

The primary outcome (hospitalization-requiring AECOPD or death from all causes within 12) will be presented as a fraction with percentage and relative risk with a 95% confidence interval. The groups will be compared using a two-sided binomial test. The same principles will be applied to secondary binomial outcomes. For the SABA pick-up rate, the incidence rate and ratios will be calculated and presented (including 95% confidence intervals) and compared using the chi-squared test. Changes in CAT and MRC (respectively) will be reported as median differences with IQR and compared within and between groups with a paired two-sided Wilcoxon signed-rank test and an unpaired two-sided Wilcoxon rank-sum test. A subgroup analysis will be performed on the primary outcome with the following subgroups: adherence group (high adherence: ≥4–5 days per week of adherence), age (≥65 years), asthma overlap, coexisting heart failure, body mass index (>30 kg/), frequent exacerbator (>1 severe exacerbation within 12 months prior to baseline), and treatment with systemic beta-2 antagonist at baseline. A *p*-value of <0.05 will be considered significant.

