### Methods for additional analyses (e.g., subgroup analyses)

Continuous baseline variables will be summarized using means, 95% confidence intervals, medians, and interquartile ranges according to distribution. Categorical variables will be compared using frequencies and proportions. All statistical tests will be two-sided, and *p*-values of <0.05 will be considered statistically significant.

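### The chi-squared test named for the SABA pick-up rate takes no account of repeat pick-ups by the same person, so its p-values are too small if pick-ups vary between persons more than Poisson

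*Protocol article*

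**What the plan says.** In the protocol article, the section on outcomes lists "SABA use/pick-up rate" as the last of six secondary efficacy endpoints. Table 2 defines it by three ATC codes and a data source: "SABA use/pick-up rate R03AC02, R03CC02, R03AC03 Danish National Prescription Registry". The time frame under that table runs "until the end of the study (12 months from randomization) for all outcomes". One participant can therefore contribute several pick-ups.

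The section on statistical methods for primary and secondary outcomes fixes the analysis of this rate: "the incidence rate and ratios will be calculated and presented (including 95% confidence intervals) and compared using the chi-squared test". This rule stands apart from the one for the binomial secondary outcomes, so the endpoint is meant as an event rate and not as the share of participants with any pick-up. The same section repeats the secondary analyses in the per-protocol and modified ITT sets. On significance, the article says: "All statistical tests will be two-sided, and *p*-values of <0.05 will be considered statistically significant".

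The article does not say whether pick-ups are totalled over participants, how the interval is computed, or how pick-ups are distributed. It mentions no count model, robust variance or other allowance for overdispersion.

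**The concern.** A chi-squared comparison of two incidence rates ordinarily takes its variance from the event totals. That is correct only if pick-ups occur independently, so that the variance of the count per person equals its mean. Reliever refills are unlikely to behave so: participants differ in how much they use, and those who collect often do so repeatedly. Allocation was by person, so the random error in the comparison is the variation between persons. A test that ignores the excess variation understates this error.

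At stake is a false claim of a difference in reliever use. The interim analysis section declines to stop for superior efficacy so that the trial has power to conclude on its secondary endpoints. The sponsor therefore means to draw inferences from endpoints such as this one.

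**Working it through.** The article gives no mean, spread or share of users for SABA pick-ups, so it has no figure for this endpoint to reproduce. Its sample size of 6,662 was derived for the primary outcome and does not enter here.

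**Inputs from the article**
- Test: chi-squared on incidence rates (statistical methods section).
- Level: 0.05 two-sided, so the critical value is 1.96, or 3.84 on the chi-squared scale.
- Size: "A total of 10,013 participants were randomized" (abstract), allocated 1:1, so n is about 5,006 per arm.

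**Assumed input.** φ is the variance-to-mean ratio of pick-ups per person. For a negative binomial count with mean μ and dispersion k, φ = 1 + kμ. For example, a mean of 3 per year with k = 1 gives φ = 1 + 1 × 3 = 4.

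**Step 1: what the test assumes.** Let X and Y be the total pick-ups in two arms with equal person-time. The statistic is (X − Y)² / (X + Y). Its denominator estimates 2nμ, which is the variance of X − Y only when φ = 1. The true variance is 2nφμ. With no treatment effect, the statistic therefore behaves as φ times a chi-squared variable on 1 degree of freedom.

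**Step 2: size of the error.** The true type I error is 2 × [1 − Φ(1.96/√φ)]. The usual Poisson rate-ratio interval has 1/√φ of the correct width on the log scale.

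| Assumed φ | 1.96/√φ | True type I error | Interval width against correct |
|---|---|---|---|
| 1.25 | 1.753 | 8% | 89% |
| 1.5 | 1.600 | 11% | 82% |
| 2 | 1.386 | 17% | 71% |
| 4 | 0.980 | 33% | 50% |
| 8 | 0.693 | 49% | 35% |

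The number of participants does not appear in the formula, so a large trial gives no protection.

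**Step 3: check by simulation.** Negative binomial counts were drawn with 5,006 per arm, no treatment effect and 4,000 replicates per case. The rejection rates at a nominal 0.05 were:

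| Mean | k | φ | Chi-squared on totals | Between-person variance |
|---|---|---|---|---|
| 4 | 0 (Poisson) | 1 | 0.047 | 0.046 |
| 2 | 0.5 | 2 | 0.165 | 0.048 |
| 2 | 1 | 3 | 0.249 | 0.049 |
| 4 | 0.5 | 3 | 0.258 | 0.050 |
| 4 | 1 | 5 | 0.382 | 0.052 |

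The simulation agrees with the formula. The chi-squared test holds its level when counts are Poisson and loses it once they are overdispersed. A comparison based on the variation between persons holds its level in every case.

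**The case against.** The strongest reply is that the article does not say that pick-ups are pooled. A chi-squared test could be the Wald or likelihood-ratio test of a person-level regression model, and the endpoint label does not exclude counting only the first pick-up. The article is also a condensed text, and the variance estimator and interval method for one secondary endpoint are commonly left to the SAP.

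Part of this stands. That the test works on totals is an inference, though it is the ordinary reading of a chi-squared comparison of incidence rates, and the article names no model from which another chi-squared statistic could come. The silence on the interval method is no fault in itself. The named test, however, is a stated choice and not an omission.

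A reader might infer four stronger things that the article does not support:

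- **That the intervals are certainly too narrow.** This follows only if they are the usual Poisson intervals. A robust or bootstrap interval would fit the same sentence.
- **That the type I error is known to be in the range of 17% to 49%.** These figures rest on assumed ratios of 2 to 8, and milder overdispersion gives 8% to 11%. Only the direction follows once the ratio exceeds 1.
- **That a few heavy users could produce a significant result.** With an assumed mean of 3 per year, each arm has about 5,006 × 3 = 15,018 pick-ups. Nominal significance then needs a net imbalance of about 1.96 × √30,036 ≈ 340. If heavy users collect 12 to 24 a year (assumed) in place of 3, that is 340/21 ≈ 16 to 340/9 ≈ 38 more such users in one arm. The issue is general variation between persons.
- **That the estimated effect is wrong.** Overdispersion does not bias the rate ratio; it affects the stated precision.

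**Conclusion.** The point holds for the named test. If pick-ups vary between persons more than Poisson, p-values for the SABA endpoint are too small in the ITT, per-protocol and modified ITT analyses alike. The conclusion rests on two assumptions: that the test is the ordinary one on event totals, and that the variance-to-mean ratio exceeds 1. Both are likely, but the article confirms neither. The size of the error is illustrative because the article gives no data on the ratio.

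The primary outcome is a yes-or-no event per person, so neither its analysis nor the sample size is touched. The interim analysis looks at the primary endpoint and mortality and does not use SABA pick-ups. This is a should-fix matter for one secondary endpoint.

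**What to change.** Replace the chi-squared test with one prespecified person-level analysis of the number of pick-ups per participant. This can be negative binomial regression, or Poisson regression with participant-level robust variance, with log person-time alive as offset. Take the rate ratio, its 95% interval and the p-value from that one model, and use it in the per-protocol and modified ITT analyses as well. State that all pick-ups in the time frame count, if that is intended.

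The cost is a change of wording in the analysis plan before the analysis. The pick-ups and dates of death come from registries that the trial already uses for its endpoints, and no new follow-up is needed.

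Adjustment for SABA pick-ups before randomization is optional. It may gain precision but is not needed to correct the variance. The data collection section refers only generally to medication details from the registries, so the sponsor should first check that the extract includes these earlier pick-ups.

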**Methods:**

Randomized controlled open-label trial. Persons aged 30 years or older with a once-daily LAMA prescription and a confirmed COPD diagnosis were recruited. Participants were randomized in a 1:1 ratio to either morning or evening LAMA administration. Complete follow-up for the primary outcome, hospitalization-requiring AECOPD, or death from all causes within 1 year was captured from the Danish National Health Register, as were patient-reported outcome assessments at 6 and 12 months.

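### The chi-squared test for the SABA pick-up rate, read as a test on total pick-ups, treats repeat pick-ups by one participant as independent; its error rate exceeds 5% if pick-ups vary between participants more than a Poisson count

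*Protocol article*

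**What the plan says.** The Outcomes section of the protocol article lists SABA pick-ups last among the secondary endpoints: "v) all-cause mortality; (vi) SABA use/pick-up rate". Table 2 names the data source as the "Danish National Prescription Registry", under three ATC codes. Its footnote sets the window: "The time frame is ≥1 day after randomization until the end of the study (12 months from randomization) for all outcomes". A participant can therefore contribute no pick-ups, one or many.

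Under Statistical methods for primary and secondary outcomes, the binary secondary outcomes follow the method of the primary outcome. SABA is then handled separately: "the incidence rate and ratios will be calculated and presented (including 95% confidence intervals) and compared using the chi-squared test". The article does not say what the chi-squared table contains or how the interval is computed, and it mentions no allowance for several pick-ups by one person. The same section repeats the secondary analyses in the modified ITT and per-protocol sets and sets significance at p<0.05. A later section adds "All statistical tests will be two-sided, and" the same threshold.

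**The concern.** The unit of randomization is the participant: "Participants were randomized in a 1:1 ratio to either morning or evening LAMA administration". The independent observations are therefore participants. A chi-squared comparison of total pick-ups over person-time takes each pick-up as a separate Poisson event. That is valid only if pick-ups per participant have a variance equal to their mean.

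The article itself gives reason to expect more spread. The only exclusion criterion is declining to take part. Participants use LAMA with or without an inhaled corticosteroid or a long-acting beta-2 agonist. Subgroups are planned for asthma overlap and for frequent exacerbators. In such a population some people are likely to collect SABA rarely and others often. A chance imbalance in a few heavy users could then be reported as a significant effect of dosing time, and the same fault would recur in all three analysis sets.

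**Working it through.** **Plan's own figure.** There is none to reproduce. The article gives no mean, variance or error rate for SABA pick-ups. Its sample size of 6,662 concerns the primary outcome and does not enter here.

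**Inputs from the article.** "A total of 10,013 participants were randomized", in a 1:1 ratio, so about 5,006 and 5,007 per arm; 12 months of follow-up; two-sided alpha of 0.05.

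**Input that is assumed.** The ratio φ = variance/mean of pick-ups per participant.

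**Formula.** Let each arm have n participants with equal follow-up, mean μ and variance φμ, and no true effect. Let S1 and S2 be the total pick-ups.

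- The test statistic is X² = (S1 − S2)² / (S1 + S2).
- The denominator is close to 2nμ, which is what the Poisson model takes as the variance of S1 − S2.
- The actual variance of S1 − S2 is 2nφμ.
- So X² behaves as φ times a chi-squared variable on 1 degree of freedom. The true error is 2 × (1 − Φ(1.96/√φ)).
- n cancels, so a larger trial gives no protection.
- An interval built on the Poisson variance has 1/√φ of the correct width.

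**Results.**

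| φ (assumed) | 1.96/√φ | True error at nominal 5% | Poisson interval as share of correct width |
|---|---|---|---|
| 1 | 1.96 | 5.0% | 100% |
| 1.25 | 1.75 | 8.0% | 89% |
| 1.5 | 1.60 | 11.0% | 82% |
| 2 | 1.39 | 16.6% | 71% |
| 3 | 1.13 | 25.8% | 58% |
| 4 | 0.98 | 32.7% | 50% |
| 6 | 0.80 | 42.4% | 41% |

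**Simulation.** Negative binomial counts were drawn for 5,006 and 5,007 participants with no true effect, 20,000 replicates per setting. Rejection rates were 8.0% (mean 1, φ = 1.25), 16.7% (mean 2, φ = 2), 32.8% (mean 3, φ = 4) and 42.1% (mean 5, φ = 6). These confirm the formula. They say nothing about which φ applies in this trial.

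**How spread produces φ.** Suppose half the participants collect none and half collect a Poisson number with mean 4. The mean is 0.5 × 4 = 2, the variance is 0.5 × (4 + 16) − 2² = 6, and φ = 6/2 = 3, with a true error of 25.8%. This is an illustration, not an estimate.

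**After the change.** With a variance for the log rate ratio estimated from participant-level counts, simulated error was 4.7% (mean 3, φ = 4) and 5.3% (mean 2, φ = 2), 3,000 replicates each.

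**Alternative reading.** If the test compares any with no pick-up, each participant counts once. Simulated error was 4.8%, assuming 60% have a pick-up. That test addresses a proportion, not the rate ratio beside which it would be reported.

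**The case against.** The article does not say that the test is on total pick-ups. The endpoint name, "SABA use/pick-up rate", leaves room for any use, and a test on any use has the right error rate. This stands as a caveat, but it does not rescue the plan. Binary outcomes are dealt with in the preceding sentence and SABA is set apart as an incidence rate, so total pick-ups is the natural reading. On the other reading, the test does not match the reported ratio.

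A reader might infer that the false-positive rate is bound to be far above 5%. The documents do not support that. They give no dispersion: at φ = 1 the test is correct, and at 1.25 the error is 8%.

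A reader might also infer that the published interval will be too narrow. That does not follow either, because the interval's method is not stated. The variance behind an interval is a detail that may properly sit in an analysis plan not shown here, and its absence is no fault.

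That defence does not reach the test itself, which the article names. It is also fair to say that this is one secondary endpoint of six. The primary outcome and the sample size are untouched.

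**Conclusion.** The point holds in conditional form. On the natural reading, the article fixes a test that ignores repeat pick-ups by the same participant, and the test is anti-conservative whenever the variance of pick-ups exceeds the mean. Under assumed ratios of 1.25, 2 and 4, the true error is about 8%, 17% and 33%, regardless of the number randomized. The interval is narrow to a matching degree (89%, 71% and 50% of the correct width) only if it rests on the same Poisson variance. On the any-versus-none reading the error rate is sound, but test and estimate do not match. The wording needs changing either way. The consequence is confined to the SABA endpoint in the ITT, modified ITT and per-protocol sets.

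**What to change.** Replace the chi-squared comparison with one participant-level analysis: the number of SABA pick-ups per participant regressed on arm, with log follow-up time as offset. Use negative binomial regression, or Poisson regression with robust or quasi-Poisson standard errors. Which of these is chosen matters less than that the variance comes from participants. Take the rate ratio, its 95% confidence interval and the p-value from that single model, and use it in all three analysis sets.

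The cost is one sentence of analysis wording and no new data. If pick-ups are overdispersed, the interval will be wider than a Poisson one, and a modest difference will be harder to declare significant.

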### Objectives

The main objective of this intervention and research protocol is to determine whether evening administration of LAMA, as opposed to morning administration, is superior for the occurrence of hospitalization-requiring AECOPD or death from all causes. The intervention will have the following secondary objectives: (1) moderate COPD exacerbations, (2) all-cause hospitalization, (3) intensive care unit (ICU) admission, (4) need for non-invasive ventilation, (5) all-cause mortality, (6) Short-Acting Beta-Agonist (SABA) use / pick up rate, and exploratory endpoints (1) change in COPD Assessment Test (CAT) score, (2) change in Medical Research Council (MRC) score, and (3) change in the “soundly sleeping” parameter of CAT.

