### Methods in analysis to handle protocol non-adherence and any statistical methods to handle missing data

Secondary analyses will include mITT and per-protocol analyses to provide a comprehensive evaluation of the study outcomes. No data on the primary outcome will be missing as national registries will be used for outcome assessment. Only self-reported outcomes such as MRC and CAT can be expected to be missing. It will be assumed all missing data will be missing at random or completely at random to allow for multiple imputations. No imputed data will be presented in the baseline table.

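### Change in MRC is summarised only by a median difference with IQR, which on a scale of a few grades can read 0 versus 0 beside a very small rank-sum p-value

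*Protocol article*

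**What the plan says.** In the protocol article, under Statistical methods for primary and secondary outcomes, the summary for the two symptom scores is fixed: "Changes in CAT and MRC (respectively) will be reported as median differences with IQR". The same sentence adds the tests, within and between groups: a "paired two-sided Wilcoxon signed-rank test and an unpaired two-sided Wilcoxon rank-sum test". Under Methods for additional analyses the threshold is general: "All statistical tests will be two-sided, and *p*-values of <0.05 will be considered statistically significant".

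No confidence interval or other effect measure is named for CAT or MRC. In the same paragraph the primary and the binary secondary outcomes get a relative risk with a 95% CI, and SABA pick-up gets a rate ratio with a 95% CI.

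The Objectives section classes these measures as "exploratory endpoints (1) change in COPD Assessment Test (CAT) score, (2) change in Medical Research Council (MRC) score", and adds "change in the “soundly sleeping” parameter of CAT". Table 3 in the Outcomes section lists the last as "Change in CAT “soundly sleeping” parameter", with no analysis method of its own. Table 2, whose title covers both secondary and exploratory endpoints, also lists CAT and MRC. Both are collected by questionnaire at 6 and 12 months.

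**The concern.** A change in grade on a short ordinal scale is a whole step, and in many cohorts most people stay where they are. A median responds only when the middle participant moves, so it can stay at 0 while a real share of one arm improves. The IQR has the same weakness at the quarter points.

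This trial is large: "A total of 10,013 participants were randomized". At that size a rank test reaches significance for modest shifts, so the information lies in the effect estimate. If that estimate prints as 0 against 0, the reader has a small p-value and cannot tell how large the effect is or which arm it favours. CAT, MRC and the sleep item are the only patient-reported symptom outcomes listed, and the Discussion rests part of its argument on morning symptoms and sleep.

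**Working it through.** The article gives no figure for CAT or MRC (no number of grades, score range, expected change or SD), so there is no figure of the plan to reproduce. All change distributions below are assumptions.

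**1. When the median is 0.** Code the change as −1 (improved), 0 or +1 (worse). The median is 0 whenever fewer than half improve and fewer than half worsen. What counts is movement in one direction, not movement as such: with 40% improved, 20% unchanged and 40% worse, 80% move and the median is still 0. Likewise, the IQR is 0 to 0 whenever fewer than 25% improve and fewer than 25% worsen.

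**2. Example.** Arm size is 10,013 / 2, about 5,006.

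| Arm (assumed) | Improved | Unchanged | Worse | Median (IQR) |
|---|---|---|---|---|
| Morning | 15% | 65% | 20% | 0 (0 to 0) |
| Evening | 22% | 60% | 18% | 0 (0 to 0) |

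Rank-sum test, comparing a random evening participant with a random morning participant:
- Evening does better: 0.22 × 0.85 + 0.60 × 0.20 = 0.307
- Morning does better: 0.15 × 0.78 + 0.65 × 0.18 = 0.234
- Tied: 1 − 0.307 − 0.234 = 0.459
- Probability of superiority: 0.307 + 0.459 / 2 = 0.5365, which is 0.0365 above 0.5
- Tie factor: 1 − (0.185³ + 0.625³ + 0.190³) = 0.743
- Standard error: √[10,013 × 0.743 / (12 × 5,006²)] = 0.00497
- z = 0.0365 / 0.00497 = 7.3, two-sided p about 2e-13

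The median of all pairwise between-arm differences is also 0, because neither direction holds half of the pairs (0.307 and 0.234). So the printed difference is 0 whether it is read as a difference of medians or as a median of differences.

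Difference in proportion improved: 0.22 − 0.15 = 0.070. SE = √[(0.22 × 0.78 + 0.15 × 0.85) / 5,006] = 0.0077. The 95% CI is 5.5 to 8.5 points.

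**3. Range over arm size and effect.** The article expects missing questionnaires ("Only self-reported outcomes such as MRC and CAT can be expected to be missing") but gives no rate.
- The same example with 1,500 per arm: medians and IQRs are still 0 (0 to 0) in both arms, p about 6e-5, and the difference in proportion improved is 7.0 points (95% CI 4.2 to 9.8).
- Smaller shift, 15/65/20 against 18/65/17, simulated 200 times at each of 2,500, 3,500 and 5,006 per arm: medians 0 and IQRs identical in every run; p < 0.05 in 94.5% to 100% of runs.
- Large shift, 20/50/30 against 45/40/15: both medians still 0 in every run, but the IQRs differ in every run (0 to 1 against −1 to 0).

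**4. Total CAT.** Changes were simulated as rounded normal values, SD 4 or 6, 3,500 per arm, 200 runs each. About 90% to 93% of participants move by at least one point. A true shift of 1 point gave a median difference of exactly −1, and a shift of 2 points exactly −2, in every run. A difference of 0 appeared in about 43% to 50% of runs at a 0.5-point shift, and in 93% to 99% at 0.3.

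**The case against.** The strongest reply is that the plan would not miss the effect. The sentence that sets the median also sets a rank-sum test, which uses the whole distribution and rejects in nearly every simulated run. A reader might infer that a real MRC benefit would be reported as no difference. The article does not support that: the benefit would be declared significant but poorly described.

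A reader might also extend the point to the total CAT score. That does not hold either. CAT is a multi-item score, and under the assumed SDs its median tracks shifts of one point or more; only shifts of about half a point or less can disappear.

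Third, the methods section names no summary for the sleep item, so no stated median is wrong there. The point reaches that item only if the CAT rule is meant to cover it.

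Fourth, the premises on MRC are not in the article, and with a large enough shift the IQRs do differ between arms. Median, IQR and rank tests are a coherent set for ordinal data, and a fuller analysis plan may add an effect estimate. This limits the weight of the point but does not remove it: the article does name the summary for MRC, and that summary can be empty just where the test is significant.

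**Conclusion.** The point holds for MRC and in a limited form. The stated summary can print 0 (0 to 0) in both arms while the planned test gives a very small p-value, leaving size and direction unreadable. In the worked example a 7.0-point difference in the proportion improved (95% CI 5.5 to 8.5) would be invisible in the reported effect, and the same holds at 1,500 per arm.

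This rests on two assumptions that the article neither states nor contradicts: that MRC has only a few whole grades, and that in each arm fewer than about a quarter improve and fewer than about a quarter worsen. If between a quarter and a half move one way, the IQR begins to show the shift but the median does not.

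Severity is low. The endpoints are exploratory, and neither the sample size nor the primary conclusion depends on them.

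**What to change.** In Statistical methods for primary and secondary outcomes, keep the Wilcoxon tests, and keep the medians with IQR as description. For MRC, add one of the following:

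- the proportions improved, unchanged and worsened by at least one grade in each arm, with the between-arm difference and its 95% CI; or
- a common odds ratio with 95% CI from an ordinal model adjusted for baseline grade.

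If the CAT rule is meant to cover the single sleep item, say so and use the same measure there. For total CAT, a between-arm difference with 95% CI is an optional addition.

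The cost is a change of wording and a little more analysis and reporting. The questionnaires and the data stay the same.
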